---

## BACKGROUND

The World Health Organization identifies trauma as a major global public health problem. Nearly 60% will experience a potentially traumatic event by the end of adolescence . For example, 40 million children aged below 15 years fall victim to violence each year. The prevalence of post-traumatic stress disorder (PTSD) in children exposed to trauma is estimated to be between 5% to 16% . It is even more common in particular populations such as refugee children . PTSD is a debilitating psychiatric condition involving distressing symptoms such as intrusions from the traumatic event, inability to be around trauma reminders, cognitive and mood changes, and arousal symptoms and associated with considerable functional impairment and comorbidity . For children with untreated PTSD, extensive data shows a significantly increased risk for substance use, suicidality, and poorer mental health/functioning  as well as impaired school performance . TF-CBT has proven effective in treating youth with PTSD and is considered first-line treatment but is rarely available in regular care.

Given the large group of afflicted and the treatment gap, action is clearly needed to increase availability. A possible solution to significantly improve access to evidence-based treatment would be the use of remotely delivered digital intervention. Internet-delivered trauma-focused CBT (iTFCBT) may also carry several other advantages compared to traditional psychological treatments (eg. less therapist time per patient, bridging geographical distances between therapist and patient, and provision of a standardized intervention). Internet-delivered treatment has shown promising results in treating adults with PTSD  and as early intervention after trauma . Furthermore, research has indicated that ICBT is an effective treatment format for children . But, to our knowledge, this project is the first large RCT to evaluate digital iTFCBT for children with PTSD.

## OBJECTIVE

### PRIMARY OBJECTIVE

There is an urgent need for evidence-based treatments for children with PTSD that can easily be made available to a large number of afflicted. The overall aim of the project is to increase the availability of evidence-based psychological treatments for adolescents with PTSD by developing and evaluating iTFCBT for this target group. The main objectives are to establish the efficacy, cost-effectiveness, and long-term effects of iTFCBT for adolescents with PTSD in an RCT (N=140) by comparing guided iTFCBT with an attention control group consisting of therapist-supported internet-delivered psychoeducation and support.

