## DESCRIPTION OF THE STUDY

This study is a single-blind, parallel-group superiority trial with an internal pilot. Study participants will be randomly assigned to 12 weeks of either iTF-CT or therapist-supported internet-delivered psychoeducation on a 1:1 ratio without restriction. To prevent potential selection bias related to the randomization procedure, we will use an external party, the Karolinska Trial Alliance (KTA, [www.karolinskatrialliance.se](http://www.karolinskatrialliance.se)) for that. Allocation concealment will be ensured through randomization after the decision to include each participant has been made. Evaluation includes efficacy, cost-effectiveness, and long-term effects. Outcome measures will be evaluated at baseline, post-treatment, 1-months (primary endpoint), and 6- and 12-months follow-up by assessors blinded to treatment allocation. To ensure blinding integrity, participants and their guardians will receive explicit instructions not to disclose which treatment they have received. After completing the assessment, the blind raters guess the participant's group allocation. If participants inadvertently disclose the treatment allocation during the assessment, another blind assessor will re-assess the diagnosis based on recordings of the clinical interviews. Participants will be recruited nationally through self- or clinician referral. Self-referral will be made available through a dedicated secure website.

The first 20 included participants will not be randomized but will be part of an internal pilot. They will be asked to participate in process evaluation interviews after treatment completion. Interviews will also be conducted with therapists and clinicians recruiting to the study and providing treatment. The aim of this is to see that the recruitment and treatment procedures are feasible and acceptable and that retention to the trial are sufficient to allow the trial to progress.

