## SAMPLE SIZE

## OUTCOME MEASURES

The power analysis for the RCT is based on the gold-standard interview CAPS-5 where a clinically significant difference in treatment effects is 10 points, which is the between groups difference we aim to detect. With a standard deviation of the CAPS-5 to be 20, this represents a standardized mean difference in terms of Cohens  $d$  of 0.5 and to use it conservatively we used Cohens  $d$  0.4 in our calculations. The estimated number needed is then  $N=240$  (moderate between-group effect size against active control condition at 1-month post-treatment; 95% power, 10% data attrition rate, and an  $\alpha$  level of 0.04). All analysis will be conducted according to the intent to treat principle and we will follow the CONSORT guidelines in reporting and analyzing the data.

The primary hypothesis (clinician-rated CAPS-5-CA) will be evaluated using a linear mixed-effects model with fixed effects of time and group, their interaction, as well as random intercept and slope. Treatment response will be defined as at least 6 points improvement on the CAPS-5 between baseline and participants' last available measurement between baseline and 12-month follow-up (adapted from Schnurr & Lunney, 2016). Secondary self-rated outcomes will be estimated using linear mixed-effects models with repeated measurements and fixed effects of time and group, their interaction, as well as a random intercept and slope.

We will follow the Consolidated Health Economic Evaluation Reporting Standards (CHEERS) guidelines to report the health economic evaluation and look at both direct costs (e.g., therapist time per patient) and other societal costs (e.g., absence from school, caregivers' absence from work). Cost differences between iTF-CBT and the active control condition will be calculated, as well as the incremental cost-effectiveness ratio (ICER). The ICER is a global estimate of cost-effectiveness and represents the additional cost that is associated with the additional clinical effect in one intervention compared with another. Intra-Class Correlations will be used to calculate Interrater agreement on the CAPS-5-CA.

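### The protocol states two unreconciled trial sizes, N=140 and N=240, and in an unadjusted comparison neither gives the stated 95% power at the effect size the protocol says it used

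*Protocol*

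**What the plan says.** Two sections of the Protocol give a total for the same trial.

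- Primary Objective: the trial is to establish efficacy, cost-effectiveness and "long-term effects of iTFCBT for adolescents with PTSD in an RCT (N=140) by comparing guided iTFCBT with an attention control group".

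- Sample Size / Outcome Measures: "The estimated number needed is then $N=240".

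The second section also gives the inputs behind its figure.

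- Target difference: "a clinically significant difference in treatment effects is 10 points, which is the between groups difference we aim to detect".

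- Spread: "With a standard deviation of the CAPS-5 to be 20", which makes the 10-point difference d = 0.5.

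- Effect size entered: "to use it conservatively we used Cohens $d$ 0.4 in our calculations".

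- Error rates and losses: "95% power, 10% data attrition rate, and an $\alpha$ level of 0.04". Whether the test is one-sided or two-sided is not stated.

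Description of the Study sets allocation "on a 1:1 ratio without restriction" and says that the first 20 participants included form an internal pilot and are not randomised. It does not say whether those 20 lie inside 140, inside 240, or outside both.

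**The concern.** Both totals stand in current protocol text and describe the same randomised comparison, so at least one of them is wrong. They differ by 100 participants. The randomised total decides when recruitment is complete and how firmly the primary question, the difference in CAPS-5-CA at 1 month after treatment, can be answered. If the trial closed at 140 and its report cited the protocol's power statement, readers would credit it with a sensitivity that an unadjusted comparison of that size does not have.

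**Working it through.** **1. Can the two totals be reconciled?**

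- Pilot added to the smaller: 140 + 20 = 160, not 240.
- Pilot taken from the larger: 240 - 20 = 220, not 140.
- Randomised against evaluable: 240 x 0.90 = 216, not 140.
- Per arm against total: 2 x 140 = 280, not 240.

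None of these bridges the gap.

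**2. The protocol's own figure of 240.** Inputs from the sample-size text: d = 0.4, power 95%, alpha 0.04, attrition 10%; 1:1 allocation from Description of the Study. Two-sidedness is my assumption. Normal approximation:

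n per arm = 2 (z_alpha + z_power)^2 / d^2

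- Two-sided, d = 0.4: 2 x (2.0537 + 1.6449)^2 / 0.16 = 171.0, so 171 per arm, 342 evaluable, 342 / 0.9 = 380 randomised.
- One-sided, d = 0.4: 2 x (1.7507 + 1.6449)^2 / 0.16 = 144.1, so 145 per arm, 290 evaluable, 290 / 0.9 = 323 randomised.
- Two-sided, d = 0.5: 2 x (2.0537 + 1.6449)^2 / 0.25 = 109.4, so 110 per arm, 220 evaluable, 220 / 0.9 = 245 randomised.

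The stated inputs do not reproduce 240. It comes close only if an input changes: d = 0.5 in place of 0.4 (245), or 80% power in place of 95% (105 per arm, 210 evaluable, 234 randomised).

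**3. Power at each stated total.** With 10% attrition, 140 leaves 140 x 0.9 / 2 = 63 per arm and 240 leaves 108. If the 20 pilot participants were counted within 140, 120 would be randomised and 54 per arm would be evaluable. Normal approximation:

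power = Phi( d x sqrt(n/2) - z_alpha )

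Worked case, N = 140, d = 0.4, two-sided: 0.4 x sqrt(31.5) = 2.245; 2.245 - 2.054 = 0.191; Phi(0.191) = 57.6%. The noncentral t gives 56.8%.

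All cases at alpha 0.04, with 10% attrition and no adjustment (normal / noncentral t):

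| Randomised | d | Two-sided | One-sided |
|---|---|---|---|
| 120 | 0.4 | 51.0% / 50.2% | 62.8% / 62.3% |
| 120 | 0.5 | 70.7% / 69.8% | 80.2% / 79.6% |
| 140 | 0.4 | 57.6% / 56.8% | 68.9% / 68.5% |
| 140 | 0.5 | 77.4% / 76.7% | 85.4% / 85.0% |
| 240 | 0.4 | 81.2% / 80.8% | 88.3% / 88.1% |
| 240 | 0.5 | 94.7% / 94.5% | 97.3% / 97.2% |

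**4. Precision.** The interval matching a two-sided alpha of 0.04 is a 96% interval, with half-width 2.0537 x 20 x sqrt(2/n). That is 7.3 points with 63 per arm and 5.6 points with 108, against a target difference of 10 points (8 points at d = 0.4).

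**5. What baseline adjustment could add.** The protocol gives no baseline-to-endpoint correlation r, so this is an assumption shown as a range. If the mixed model recovered the precision of a covariance analysis, d would be divided by sqrt(1 - r^2). For 140 randomised, 63 per arm, two-sided alpha 0.04 (noncentral t):

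| r | d = 0.4 | d = 0.5 |
|---|---|---|
| 0.3 | 61% | 81% |
| 0.5 | 70% | 88% |
| 0.6 | 77% | 92% |
| 0.7 | 86% | 97% |
| 0.8 | 95% | over 99% |

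**The case against.** The strongest reply is that 57% is one corner of a range. It rests on a two-sided test that the protocol does not specify, on d = 0.4 rather than the 10-point difference the protocol says it aims to detect, on an unadjusted comparison although a mixed model with a baseline measurement is planned, and on all 140 being randomised. This stands: the figure must carry its conditions. It does not rescue the text. Every unadjusted figure for 140 falls short of 95%, the most favourable being 85% (one-sided, d = 0.5), and credit for baseline would need a correlation that the protocol does not state.

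A second reply is that the sample-size section governs and that 140 is a parenthesis in the objectives, perhaps a slip. That may be so, but the document does not say so, and step 2 shows that 240 does not follow from its own inputs either.

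Two stronger readings are tempting and are not supported.

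- A reader might infer that the protocol mixes two designs, because d = 0.5, 80% power, two-sided alpha 0.05 and 10% attrition gives 140 to 143 depending on method. Neither 80% power nor alpha 0.05 appears in the document. A leftover figure or a one-digit slip explains 140 equally well.
- A reader might infer that two targets invite stopping on the strength of accumulating results. The protocol describes no interim efficacy look, the Time Plan places the statistical analyses after the last participant's post-assessment, and outcome assessors are blinded.

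Nor can the conflict be left to a statistical analysis plan: no later document makes two different stated totals both correct.

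**Conclusion.** The contradiction is established: 140 and 240 are both stated, nothing reconciles them, and the pilot does not explain the difference. Assuming a two-sided test at alpha 0.04, 10% attrition and an unadjusted comparison, 140 randomised gives about 57% power at d = 0.4 and about 77% at d = 0.5. One-sided, these become about 69% and 85%. If the pilot sits inside the 140, two-sided power at d = 0.4 is about 50%.

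On the same two-sided assumptions, 240 gives about 81% at d = 0.4 and 94-95% at d = 0.5. The 95% claim is therefore close to correct for 240 only at d = 0.5, which is not the value the protocol says it entered. The documents do not show which total is intended or how either arose. This should be corrected before the protocol is relied on, because a basic design quantity is wrong as written and restating it is cheap.

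**What to change.** - State one number of randomised participants, identical in Primary Objective and in the sample-size text.
- Say that the 20 non-randomised pilot participants are not part of that number.
- State whether the primary test is one-sided or two-sided.
- Choose one effect size for the power statement and replace the 95% with the power that the chosen number delivers at alpha 0.04. For a two-sided, unadjusted test with 10% attrition: N=140 gives about 57% at d = 0.4 or 77% at d = 0.5; N=240 gives about 81% at d = 0.4 or 94-95% at d = 0.5.
- If credit is taken for baseline adjustment, state the assumed correlation and its basis.
- If alpha is to move from 0.04, make that change explicitly and separately, not as a by-product of restating the power.

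The cost is protocol wording and a lower stated power in most of these cases. If 95% at d = 0.4 is to be kept, the cost is recruitment: about 380 randomised two-sided, or 323 one-sided, without baseline adjustment.

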### Research questions:

1. Is guided iTFCBT more efficacious than an active control condition (therapist-supported internet-delivered psychoeducation and support) in regard to reduction of blinded assessor rated PTSD symptom severity 1-month post-treatment?
2. Is guided iTFCBT more cost-effective than an active control condition (therapist-supported internet-delivered psychoeducation and support) in regard to reduction of blinded assessor rated PTSD symptom severity 1-month post-treatment?

3. Are the therapeutic gains of iTF-CBT maintained at long term follow up (6 and 12 months after treatment)?
4. How do children, parents and therapists perceive iTF-CBT?

## DESCRIPTION OF THE STUDY

This study is a single-blind, parallel-group superiority trial with an internal pilot. Study participants will be randomly assigned to 12 weeks of either iTF-CT or therapist-supported internet-delivered psychoeducation on a 1:1 ratio without restriction. To prevent potential selection bias related to the randomization procedure, we will use an external party, the Karolinska Trial Alliance (KTA, [www.karolinskatrialliance.se](http://www.karolinskatrialliance.se)) for that. Allocation concealment will be ensured through randomization after the decision to include each participant has been made. Evaluation includes efficacy, cost-effectiveness, and long-term effects. Outcome measures will be evaluated at baseline, post-treatment, 1-months (primary endpoint), and 6- and 12-months follow-up by assessors blinded to treatment allocation. To ensure blinding integrity, participants and their guardians will receive explicit instructions not to disclose which treatment they have received. After completing the assessment, the blind raters guess the participant's group allocation. If participants inadvertently disclose the treatment allocation during the assessment, another blind assessor will re-assess the diagnosis based on recordings of the clinical interviews. Participants will be recruited nationally through self- or clinician referral. Self-referral will be made available through a dedicated secure website.

The first 20 included participants will not be randomized but will be part of an internal pilot. They will be asked to participate in process evaluation interviews after treatment completion. Interviews will also be conducted with therapists and clinicians recruiting to the study and providing treatment. The aim of this is to see that the recruitment and treatment procedures are feasible and acceptable and that retention to the trial are sufficient to allow the trial to progress.

Consecutive applicants referred to the study are assessed for eligibility. Interested applicants are screened on the telephone after completion of screening measures for PTSD, and eligible youths and their families are invited to a psychiatric assessment via video-conferencing or face-to-face. The aim of this visit is ensuring eligibility by verification that PTSD is the primary diagnosis and other inclusion/exclusion criteria, assess severity of PTSD symptoms, and assess for comorbidity. The gold standard clinical interview CAPS-5-CA that assesses past month diagnosis of PTSD and PTSD symptom severity will be used to ensure validity and reliability of the PTSD diagnosis. The interview will also include the child version of the Mini International Neuropsychiatric Interview (MINI-KID). The assessor also provides detailed information about the study and treatment including objectives, benefits, risks, and requirements imposed by the study during this visit. The information is also provided in writing. If the applicant is eligible for the study, the study participant and guardian sign informed consent digitally during this visit.

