## PRIMARY MEASURES

Feasibility will be assessed by evaluating the study procedures and provision of the treatment using the RE-AIM framework, focusing on the intervention's reach (percentage eligible/excluded, reasons for refusal or exclusion), effectiveness (symptom reduction and impact on quality of life), adoption (attrition, adherence, client satisfaction), implementation (clinician resources), and maintenance (effects on symptom measures and measures of quality of life at the 6-month follow-up).

Treatment acceptability will be defined in accordance to the definition by Sekhon et al. (2017): "the extent to which people delivering or receiving a healthcare intervention consider it to be appropriate, based on anticipated or experienced cognitive and emotional responses to the intervention". This definition considers acceptability to consist of seven component constructs: affective attitude, burden, perceived effectiveness, ethicality,

intervention coherence, opportunity costs, and self-efficacy. We consider the proportion of participants that go through the entire treatment period, adverse events related to the treatment, number of dropouts and number of individuals offered the intervention but declined part of treatment acceptability. Qualitative interviews will be conducted and scheduled separately post-treatment with a focus on acceptability. Client Satisfaction Questionnaire (CSQ-8) will be used to assess patient satisfaction with treatment . Data on adverse events will be collected each treatment week using a standardized checklist (Safety Monitoring Uniform Report Form).

The primary outcome measure will be CAPS-5-CA, the gold standard clinical interview for PTSD that assess PTSD symptom severity and past month diagnosis of PTSD. CAPS-5-CA assesses the 20 DSM-5 PTSD symptoms, the onset and duration of symptoms, subjective distress, impact of symptoms on social and occupational functioning, improvement in symptoms since a previous CAPS administration, overall response validity, overall PTSD severity, and specifications for the dissociative subtype of PTSD (depersonalization and derealization).

Secondary outcome measures are self-rated PTSD symptom severity, other mental health problems, clinician-rated symptom improvement, global functioning, health-related quality of life, cost data, therapeutic alliance, treatment credibility, client satisfaction, adverse events.

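### The rule for in-interview disclosure re-rates only the diagnosis, so it does not protect the severity score that is the primary outcome

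*Protocol*

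**What the plan says.** The trial is single-blind, and its protection lies with the assessors. The Description of the Study has outcomes rated at baseline, post-treatment, 1 month and "6- and 12-months follow-up by assessors blinded to treatment allocation". Participants and guardians are told not to reveal their treatment. A check on blinding follows each interview: "After completing the assessment, the blind raters guess the participant's group allocation".

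The same section gives the remedy for a breach. The trigger is "If participants inadvertently disclose the treatment allocation during the assessment". The action is that "another blind assessor will re-assess the diagnosis based on recordings of the clinical interviews".

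The outcome to be protected is defined elsewhere. The first research question asks whether iTF-CBT is superior "in regard to reduction of blinded assessor rated PTSD symptom severity 1-month post-treatment". Primary Measures states: "The primary outcome measure will be CAPS-5-CA, the gold standard clinical interview for PTSD that assess PTSD symptom severity and past month diagnosis of PTSD". The analysis text under Sample Size / Outcome Measures adds: "The primary hypothesis (clinician-rated CAPS-5-CA) will be evaluated using a linear mixed-effects model with fixed effects of time and group". The power calculation in that section targets a 10-point difference with a standard deviation of 20.

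**The concern.** The remedy names one product of the interview (the diagnosis), while the primary comparison uses another (the severity score). Staff who follow the rule to the letter would obtain a new diagnosis and leave the severity score of the now unblinded first assessor untouched.

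The source material raises a second problem. The breach happens during the assessment, and the re-rating is made from recordings of the interviews. Unless the disclosure is cut out or fell outside the recorded part, the second assessor hears the same words and is unblinded too. In that case the rule might fail even for the diagnosis.

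Participants are not described as blinded and are asked to keep their treatment to themselves, so assessor blinding is the main defence of an interview-rated outcome against detection bias. Treatment response (at least 6 points of improvement) and the cost-effectiveness question also rest on severity.

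**Working it through.** The point turns on wording, and the plan gives no figure to reproduce. I first set the texts side by side and then give an illustration of size.

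**Comparison of the texts**

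1. *What is re-rated.* The Description of the Study names the diagnosis. No section of the protocol provides for re-rating of severity.
2. *What is analysed.* The research question concerns "reduction of blinded assessor rated PTSD symptom severity 1-month post-treatment". The mixed model and the 10-point target both require a continuous score.
3. *Whether the two terms are interchangeable.* The protocol lists diagnosis and severity as separate outputs of the CAPS-5-CA in four places: the eligibility text in the Description of the Study, Primary Measures, the list of Outcome Measures, and Inclusion Procedure. The narrower word in the disclosure rule therefore cannot safely be read as covering both.
4. *What the second assessor hears.* The disclosure occurs in the assessment and the re-rating uses the recording. No editing is described, and none is ruled out.
5. *Which score enters the model after a disclosure.* This is not stated.

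From items 1 to 3, the safeguard as written does not cover the primary outcome. From items 4 and 5, a blinded severity score may be unavailable, and an unblinded one may be used.

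**Illustration of size**

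Inputs from the protocol: standard deviation 20, target difference 10 points, alpha 0.04 (taken as two-sided) and attrition 10%. Total N is 240 in the sample size text and 140 under Primary Objective, so both are shown. The numbers analysed are 240 × 0.9 = 216 and 140 × 0.9 = 126.

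Assumed inputs, not in the documents: f, the share of ratings in each arm made after a disclosure, 5% to 20%; and b, the net between-arm shift per disclosed rating, 2 to 6 points.

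Bias in the mean difference = f × b:
- lowest: 0.05 × 2 = 0.1 points, or 0.1 / 10 = 1% of the target
- highest: 0.20 × 6 = 1.2 points, or 1.2 / 10 = 12% of the target

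Standard error of a simple two-group difference = 20 × √(4/N):
- N = 216: 20 × √(4/216) = 2.72
- N = 126: 20 × √(4/126) = 3.56

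Two-sided type I error under this bias = 1 − Φ(z − bias/SE) + Φ(−z − bias/SE), where z is the critical value for alpha 0.04:

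| N analysed | bias 0.1 | bias 0.4 | bias 0.8 | bias 1.2 |
|---|---|---|---|---|
| 216 | 0.0401 | 0.0422 | 0.0487 | 0.0597 |
| 126 | 0.0401 | 0.0413 | 0.0450 | 0.0514 |

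This uses a plain comparison at one time point, not the planned mixed model, and serves only to show the order of magnitude.

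**The case against.** The best defence is that diagnosis is loose wording for the whole interview. The CAPS-5-CA yields both outputs from one administration, so a second assessor working through the recording could readily score severity as well. The protocol also plans intra-class correlations for agreement on the CAPS-5-CA, a statistic normally applied to scores, which suggests that second ratings of the score are contemplated. This is a fair reading of what may be intended. It does not settle what the rule requires, because the protocol elsewhere treats the two outputs as distinct, and the agreement analysis is not linked to disclosures.

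A reader might go further and infer that the unblinded severity score definitely stays in the primary analysis. The documents do not support that. No text says which score is used, and keeping the unblinded one would conflict with the primary question, which specifies a blinded rating. Likewise, a reader might take it as fact that the second assessor hears the disclosure. That is only a reasonable inference: the recording might be edited, or the remark might fall outside the recorded part.

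It can also be said that the choice of score belongs in the statistical analysis plan, which was not available for this review. That is true of the analysis step but not of trial conduct. What is re-rated, and from what material, is fixed in the protocol. If severity is not re-rated, an analysis plan may have no blinded score to specify.

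Finally, the instructions not to disclose lower the risk, and the allocation guesses help to detect failures of blinding. Both points stand, but neither supplies a replacement for a compromised score.

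**Conclusion.** The point holds in this form: the disclosure rule covers the diagnosis and not the severity score on which the primary comparison rests, so an unblinded severity score may remain in the primary analysis, and the re-rating itself may not be blind. The mismatch in wording is certain. The consequence is possible, not established.

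The size cannot be derived from the documents. Under the assumed disclosure rates and shifts, the bias is about 0.1 to 1.2 points against a 10-point target, and type I error rises from 0.04 to at most about 0.060 with 216 analysed or 0.051 with 126. Larger figures are tempting. With a shift of 5 points in each arm, in opposite directions, and 20% disclosure in both, the bias would be 2 × 0.20 × 5 = 2.0 points. Nothing in the documents supports full opposite shifts in both arms. That any bias favours iTF-CBT is also an assumption about how raters behave.

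The likely effect is modest, but the rule protects the primary outcome and is easily corrected, so it should be amended.

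**What to change.** Amend the disclosure rule in the Description of the Study along these lines: *If the allocation is disclosed during an assessment, a second blinded assessor re-rates the full CAPS-5-CA (all symptom items, total severity and diagnosis) from the recording after the disclosure has been removed. The re-rated severity score replaces the original score in the primary analysis. The number of disclosures is reported by arm.*

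I would not add a sensitivity analysis that leaves out the affected interviews. Disclosure happens after randomisation and may differ between arms, so excluding on it could itself introduce bias and sits poorly with the protocol's intention-to-treat commitment.

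The cost is a little editing of recordings and some extra scoring time. The recordings and the second assessor are already part of the plan.
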